**Table 3. Schedule of Activities: Dose Expansion (Part 2)**

| Visit Identifier                                                                                                                                                             | Screening
(≤28 days
prior to
Cycle 1,
Day 1) a | Cycle 1
(28 days)                                                                                                                     |        | Cycle 2
(28 days) |        | Cycles 3+,
(every 28 days) |        | (EOT) b | Post-
Treatment
Follow-up
(28 days
after EOT) c | Long-
Term
Follow-
up |
|------------------------------------------------------------------------------------------------------------------------------------------------------------------------------|-----------------------------------------------------------------------|------------------------------------------------------------------------------------------------------------------------------------------|--------|----------------------|--------|-------------------------------|--------|--------------------|------------------------------------------------------------------------|--------------------------------|
|                                                                                                                                                                              |                                                                       | Day 1                                                                                                                                    | Day 15 | Day 1                | Day 15 | Day 1                         | Day 15 |                    |                                                                        |                                |
| Visit Window                                                                                                                                                          |                                                                       | ±2D                                                                                                                                      | ±2D    | ±2D                  | ±2D    | ±2D                           | ±2D    | ±7D                | +7D                                                                    |                                |
| PF-07248144
administration                                                                                                                                                |                                                                       | Orally, QD continuously.                                                                                                                 |        |                      |        |                               |        |                    |                                                                        |                                |
| fulvestrant administration p
(Part 2B )                                                                                                                        |                                                                       | Intramuscularly, 500 mg on C1D1, C1D15, C2D1 and once
monthly thereafter.                                                             |        |                      |        |                               |        |                    |                                                                        |                                |
| Tumor assessments:
CT/MRI Scans of chest,
abdomen, pelvis, any
clinically indicated sites of
disease; clinical evaluation
of superficial disease q | X                                                                     | Performed every 8 weeks (±7 days) from C1D1 for the first
48 weeks and then every 12 weeks (±7 days) thereafter for up
to 2 years. |        |                      |        |                               |        | X                  |                                                                        |                                |
| Other clinical assessments                                                                                                                                            |                                                                       |                                                                                                                                          |        |                      |        |                               |        |                    |                                                                        |                                |
| Survival follow-up r                                                                                                                                              |                                                                       |                                                                                                                                          |        |                      |        |                               |        |                    | X                                                                      | X                              |
| Adverse event monitoring s                                                                                                                                        |                                                                       | Continuous.                                                                                                                              |        |                      |        |                               |        |                    |                                                                        |                                |
| Pharmacokinetics blood
sampling                                                                                                                                           |                                                                       | See Pharmacokinetic and Biomarker Sampling table below.                                                                  |        |                      |        |                               |        |                    |                                                                        |                                |
| Biomarker Sampling                                                                                                                                                           |                                                                       | See Pharmacokinetic and Biomarker Sampling table below .                                                                 |        |                      |        |                               |        |                    |                                                                        |                                |

- a. **Screening:** To be obtained within 28 days prior to C1D1.
- b. **EOT Visit:** Visit to be performed as soon as possible after the last dose of study intervention and prior to initiation of any new anti-tumor therapy. Obtain assessments if not completed in the last week on study (or within 6 weeks for tumor assessments).
- c. **Post-Treatment Follow up:** At least 28 calendar days, and no more than 35 calendar days after discontinuation of study intervention, participants will return to undergo review of concomitant treatments, vital signs, and assessment for resolution of any treatment related AEs. Participants continuing to experience treatment-related toxicity after Post-Treatment Follow-up Visit will continue to be followed at least every 28 days until resolution or determination, in the clinical judgment of the investigator, that no further improvement is expected; these may be conducted via telephone.
- d. **Informed Consent:** Must be obtained prior to undergoing any study specific procedures.
- e. **Medical/Oncological History:** To include information on oncology disease including details of diagnosis and prior anticancer treatments (systemic treatment, prior surgery and radiotherapy, etc). When available primary diagnosis history should also include known molecular characteristics of the participant's tumor including mutations, amplifications, etc.

**Table 3. Schedule of Activities: Dose Expansion (Part 2)**

|                  |                                                                       | Cycle 1
(28 days) |        | Cycle 2
(28 days) |        | Cycles 3+,
(every 28 days) |        |                    |                                                                        |                                |
|------------------|-----------------------------------------------------------------------|----------------------|--------|----------------------|--------|-------------------------------|--------|--------------------|------------------------------------------------------------------------|--------------------------------|
| Visit Identifier | Screening
(≤28 days
prior to
Cycle 1,
Day 1) a | Day 1                | Day 15 | Day 1                | Day 15 | Day 1                         | Day 15 | (EOT) b | Post-
Treatment
Follow-up
(28 days
after EOT) c | Long-
Term
Follow-
up |
| Visit Window     |                                                                       | ±2D                  | ±2D    | ±2D                  | ±2D    | ±2D                           | ±2D    | ±7D                | +7D                                                                    |                                |

- f. **Physical Examination:** Full physical exam at Screening and End of Treatment, brief physical exam at all other timepoints. A symptom-directed exam and an assessment for emergent toxicities or changes from prior visits conducted by a physician, trained physician's assistant or nurse practitioner, as acceptable according to local regulation.
- g. **Vital Signs:** Include oral temperature, pulse rate (PR), respiration rate, blood pressure (BP), and SpO2. BP and PR to be recorded in the sitting position or semi-recumbent position (same position should be maintained throughout the study) after approximately 5 minutes of rest.
- h. **ECOG Performance Status:** ECOG performance scale is available in [Section 10.12](#).
- i. **Contraception check:** The investigator or his or her designee, in consultation with the participant, will confirm that the participant has selected an appropriate method of contraception for the individual participant [and his or her partner(s)] from the permitted list of contraception methods and will confirm that the participant has been instructed in its consistent and correct use. The investigator or designee will inform the participant of the need to use highly effective contraception consistently and correctly and document the conversation and the participant's affirmation in the participant's chart (participants need to affirm their consistent and correct use of at least 1 of the selected methods of contraception). In addition, the investigator or designee will instruct the participant to call immediately if the selected contraception method is discontinued or if pregnancy is known or suspected in the participant or partner.
- j. **Concomitant Treatments:** All concomitant medications and nondrug supportive interventions should be recorded on the CRF.
- k. **Hematology, Blood Chemistry, Coagulation, and Urinalysis:** No need to repeat on C1D1 if baseline assessment performed within 7 days prior to that date (see [Section 10.2](#) for a complete list of clinical laboratory tests).
- l. **Pregnancy Test:** Pregnancy tests may be urine or serum tests, but must have a sensitivity of at least 25 mIU/mL. Pregnancy tests will be performed in WOCBP. Following a negative pregnancy test result at screening, appropriate contraception must be commenced and a second negative pregnancy test result will be required at the baseline visit prior to the participant's receiving the study treatment. Pregnancy tests will also be done whenever 1 menstrual cycle is missed during the active treatment period (or when potential pregnancy is otherwise suspected) and at the end of the study. Pregnancy tests may also be repeated if requested by IRBs/ECs or if required by local regulations.
- m. **Standard 12 Lead ECG:** ECGs will be collected at times specified in the SoA. The Screening ECG will be a single 12-lead ECG. At all other times, at each time point, 3 consecutive 12 lead ECGs (triplicate) will be performed approximately 2 minutes apart to determine mean QTcF interval. ECG on Days 1 and 15 of cycle 1 will be collected prior to dosing. ECGs on Day 1 of each cycle ≥2 will be collected prior to dosing, and at the EOT visit. All 12 lead ECGs should be confirmed by a qualified individual at the institution. If the mean QTcF is prolonged (≥45 msec from the baseline or >500 msec), the ECGs should be reevaluated by a qualified individual at the institution for confirmation. Additional triplicate ECGs may be performed as clinically indicated. For the food effect substudy, additional ECGs should be collected at Cycle 1 Day -7: at predose, 1 hr and 2 hr postdose. After predose, a window of ±10% time is allowable.
- n. **Viral Disease Screening Tests:** HbsAg, HBcAb, anti-HBs, HCVAb, and HIV to be conducted by local laboratory where required by local regulations or if warranted by participant history.
- o. **Registration:** Participant enrollment number and dose level allocation assigned by Pfizer Inc.
- p. **For Part 2B** [REDACTED]: fulvestrant to be administered in combination with PF-07248144 (Part 2B) [REDACTED]. Detailed administration information can be found in the fulvestrant (Faslodex) USPI, and country-specific label.

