### 6.1.1. Administration

#### 6.1.1.1. PF-07248144

Participants will swallow PF-07248144 whole and will not manipulate or chew the study intervention prior to swallowing. PF-07248144 will initially be administered QD by mouth for all cohorts on a continuous basis.

[REDACTED]

[REDACTED]

[REDACTED]

[REDACTED]

**6.1.1.6.** [REDACTED]

For all participants in the food effect cohort (a subset of Part 2A), PF-07248144 will be administered following an overnight fast of at least 10 hours on Cycle 1 Day-7 and Cycle 1 Day 1. On Cycle 1 Day -7 (Fed state) a test breakfast meal (described below) will be provided and must be consumed over 30 minutes. PF-07248144 will be administered with approximately 8oz (240 mL) of water 30 minutes after the start of the meal. No additional food will be allowed until at least 4 hours postdose. On Cycle 1 Day 1, patients will receive another single oral dose of PF-07248144 under fasted condition following an overnight fast of at least 10 hours. PF-07248144 will be administered with 8 oz (240 mL) of water. No food will be allowed for an additional 4 hours postdose. For either treatment day, water will be allowed ad libitum except for 1 hr before and 1 hr after drug administration. Starting from Cycle 1 Day 2 onwards, PF-07248144 will be administered QD with at least 8 oz (240 mL) of water on an empty stomach, with no food or liquids other than water for 2 hours before and 2 hours following dosing.

[REDACTED]

Substitutions to this test meal can be made after discussion with the sponsor, as long as the meal provides a similar amount of calories from protein, carbohydrate, and fat and has comparable meal volume and viscosity (if substitutions are made, the contents of the meal will be documented by a dietitian or designate to confirm it matches the FDA requirements for protein, carbohydrate and fat described above). However, it is understood that some participants may not be able to

consume the entire meal. Study staff should record the percent of the test meal breakfast and the time it takes to be consumed.

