### 8.2.3. Electrocardiograms

Standard 12-lead ECGs utilizing limb leads (with a 10-second rhythm strip) should be collected at times specified in the [SoA](#) section of this protocol using an ECG machine that automatically calculates the heart rate and measures PR, QT, and QTcF intervals and QRS

complex. Alternative lead placement methodology using torso leads (eg, Mason-Likar) is not recommended given the potential risk of discrepancies with ECGs acquired using standard limb lead placement. All scheduled ECGs should be performed after the participant has rested quietly for at least 10 minutes in a supine position.

At each time point (see the [SoA](#)), 3 consecutive ECGs will be performed at approximately 2 minutes apart to determine the mean QTcF interval.

To ensure safety of the participants, a qualified individual at the investigator site will make comparisons to baseline measurements. Additional ECG monitoring will occur if a) the mean value from the triplicate measurements for any postdose QTcF interval is increased by  $\geq 60$  msec from the baseline **and** is  $> 450$  msec; or b) an absolute QTcF value is  $\geq 500$  msec for any scheduled ECG. If either of these conditions occurs, then a single ECG measurement must be repeated at least hourly until QTcF values from 2 successive ECGs fall below the threshold value that triggered the repeat measurement. In addition, if verified QTcF values continue to exceed the criteria above, immediate correction for reversible causes including electrolyte abnormalities, hypoxia and concomitant medications for drugs with the potential to prolong the QTcF interval should be performed.

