##### Safety QTc Assessment

| Degree of Prolongation | Mild (msec) | Moderate (msec) | Severe (msec) |
|------------------------|-------------|-----------------|---------------|
| Absolute value         | >450-480    | >480-500        | >500          |
| Increase from baseline |             | 30-60           | >60           |

In addition, the number of participants with uncorrected QT values >500 msec will be summarized.

If more than 1 ECG is collected at a nominal time after dose administration (for example, triplicate ECGs), the mean of the replicate measurements will be used to represent a single observation at that time point. If any of the 3 individual ECG tracings has a QTc value >500 msec, but the mean of the triplicates is not >500 msec, the data from the participant's individual tracing will be described in a safety section of the CSR in order to place the >500 msec value in appropriate clinical context. However, values from individual tracings within triplicate measurements that are >500 msec will not be included in the categorical analysis unless the average from the triplicate measurements is also >500 msec. Changes from baseline will be defined as the change between the postdose QTc value and the average of the time-matched baseline triplicate values on Day 1, or the average of the predose triplicate values on Day 1.

In addition, an attempt will be made to explore and characterize the relationship between plasma concentration and QT interval length using a PK/PD modeling approach. If a PK/PD relationship is found, the impact of participant factors (covariates) on the relationship will be examined.

The analysis of ECG results will be based on participants in the safety analysis set with baseline and on-treatment ECG data. Baseline is defined as Cycle 1 Day 1 predose.

ECG measurements (an average of the triplicate measurements) will be used for the statistical analysis and all data presentations. Any data obtained from ECGs repeated for safety reasons after the nominal time-points will not be averaged along with the preceding triplicates. Interval measurements from repeated ECGs will be included in the outlier analysis (categorical analysis) as individual values obtained at unscheduled time points.

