### **2.3.3. Baseline Variables**

Baseline characteristics will be collected according to Schedule of Activities as specified in the protocol. No baseline variable will be used for stratification or as covariates for the primary statistical analysis. Unless otherwise specified, the baseline value is defined as the value collected at the time closest to, but prior to, starting the study intervention administration in the first cycle.

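### For the food-effect subset, the ECG analysis baseline (Cycle 1 Day 1 predose) falls a week after the first dose, so the Day -7 post-dose QTc readings precede their own reference

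*Protocol*

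**What the plan says.** **Dosing.** Protocol Sections 4.1 and 6.1.1.6 and Table 5 give food-effect participants a first dose, fed, on Cycle 1 Day -7. A second dose, fasted, follows a week later: "On Cycle 1 Day 1, patients will receive another single oral dose of PF-07248144 under fasted condition".

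**ECG schedule in Part 2.** Table 3, footnote m, makes every ECG other than the screening one a triplicate. In Cycle 1, "ECG on Days 1 and 15 of cycle 1 will be collected prior to dosing"; after that, "ECGs on Day 1 of each cycle ≥2 will be collected prior to dosing, and at the EOT visit". The subset has extra readings: "For the food effect substudy, additional ECGs should be collected at Cycle 1 Day -7: at predose, 1 hr and 2 hr postdose".

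**Baseline for analysis.** Section 9.4.5.1 states "Baseline is defined as Cycle 1 Day 1 predose", with no exception for the subset. The same section takes QTc change against "the average of the time-matched baseline triplicate values on Day 1, or the average of the predose triplicate values on Day 1". SAP Section 5.2.4 repeats the Cycle 1 Day 1 predose baseline, though its time-matched option is placed on Day -1.

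**Baseline in conduct.** Footnote m, Section 7.1 and Section 8.2.3 all use changes in QTcF from baseline. Section 8.2.3 says that "a qualified individual at the investigator site will make comparisons to baseline measurements". None of the three points to the definition in Section 9.4.5.1.

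**The concern.** A change from baseline should compare a reading taken under treatment with one taken before treatment began. For most participants Cycle 1 Day 1 predose is that pre-treatment reading. For the food-effect subset it is not: it comes after a dose, and after the 1 h and 2 h ECGs that it is meant to serve as reference for.

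Section 9.4.5.1 tabulates the largest increase in QTc from baseline in categories and summarises change by time point. For the Day -7 post-dose readings a programmer following the text has two choices. One is to subtract a later value. The other is to treat the readings as pre-baseline and leave them out of the change tables. Either way the natural comparator, a triplicate taken the same morning before any drug, is collected and then given no role as reference. These are also the only Part 2 readings scheduled within hours after a dose.

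**Working it through.** The plan gives no figure to reproduce. The check is a timeline, a count and a half-life calculation.

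**1. Timeline of scheduled Part 2 ECGs (Table 3, ECG row and footnote m)**

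| ECG | Relation to dosing | Food-effect subset: before or after the Section 9.4.5.1 baseline |
|---|---|---|
| Screening (single) | before any drug | before |
| Day -7 predose (subset only) | before any drug | before |
| Day -7, 1 h and 2 h (subset only) | after the first dose | **before** |
| Cycle 1 Day 1 predose | about 7 days after the first dose | is the baseline |
| Cycle 1 Day 15 predose | on treatment | after |
| Day 1 predose, Cycles ≥2 | on treatment | after |
| End of treatment | not timed to a dose | after |

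Day -7 to Day 1, with no Day 0 (assumed, as is usual), is 7 days = 168 h.

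**2. Does the time-matched option rescue the comparison?** No. In Part 2 the Day 1 ECG is predose only, so no 1 h or 2 h value exists on Day 1 to match with. The SAP's Day -1 alternative has no ECG in Table 3 either.

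**3. How many readings?** About 6 participants × 2 post-dose time points = about 12 triplicates. The table shows no other scheduled Part 2 ECG timed shortly after a dose.

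**4. Is the Day 1 predose value contaminated by the first dose?** The fraction of drug remaining is 0.5^(168 h / half-life).

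- Half-life 12 h, the model-based prediction at 8 mg in Section 4.3.1: 168/12 = 14 half-lives, 0.5^14 = 0.00006, or 0.006%.
- Half-life 24 h (assumed): 0.5^7 = 0.008, or 0.8%.
- Half-life 48 h (assumed): 0.5^3.5 = 0.088, or 8.8%.

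At the only half-life the documents give, carry-over is negligible. The fault is one of order and pairing.

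**5. After the fix.** With Day -7 predose as reference, both Day -7 post-dose time points follow their baseline, and no further ECG is needed.

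**The case against.** The strongest reply is that little turns on this. It concerns about 6 people in a descriptive analysis with no hypothesis test. In Part 1 all participants have ECGs at 1 h and 2 h on Days 1 and 15, at doses up to 15 mg against 5 mg in Part 2A. The Day -7 readings follow a single fed dose and fall before the reported median Tmax of 3 h. Because Day 1 predose is almost drug-free at the predicted half-life, it is also a serviceable reference for the subset's later visits. All of that stands and limits the weight of the point. It does not make a reference taken afterwards the right one for the Day -7 readings.

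A reader might infer more than the documents support:

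- **That the on-site QTcF checks cannot be applied on Day -7.** The Day 1 predose definition sits only in the analysis section. On Day -7 the site holds a screening ECG and a predose triplicate, and the absolute limits need no baseline. The reference is unclear for this subset; it is not shown to be missing.
- **That the SAP contradicts itself.** SAP Section 2.3.3 uses "the value collected at the time closest to, but prior to, starting the study intervention administration in the first cycle", but as a default that gives way where something else is specified. The ECG rule in SAP Section 5.2.4 is such a specification.
- **That the Day -7 readings are removed.** No text excludes them. Absolute QTc categories and summaries can still use them.
- **That the Day 1 value is spoiled by residual drug.** The half-life arithmetic does not support this at the predicted value.

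One limit on certainty remains. Section 4.3.8, to which the food-effect details are referred, is blacked out, so a substudy-specific ECG reference there cannot be ruled out. The visible text of Section 9.4.5.1 does not point to one.

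**Conclusion.** The point holds in a limited form. Section 9.4.5.1 fixes a baseline that, for the food-effect subset, is measured about a week after first exposure and after the Day -7 post-dose ECGs. Followed literally, it gives those readings a badly ordered change from baseline or none. This is a rule stated wrongly for one subset, not a detail left to the SAP, and SAP Section 5.2.4 repeats it.

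The size is about 12 triplicates, all of the scheduled Part 2 ECGs timed shortly after a dose, and the effect is confined to descriptive change-from-baseline QTc output. The planned concentration–QT modelling is not counted here, because the protocol does not say whether it uses change from baseline.

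The conclusion rests on the subset being about 6 as planned, on Day -7 being the first dose as the dosing sections say, and on no contrary rule standing in the redacted text. The change is worth making because it is cheap and the correct comparator is already collected.

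**What to change.** In Section 9.4.5.1, and in the matching text of SAP Section 5.2.4, define the analysis baseline for ECG parameters as the mean of the last triplicate before the first dose of PF-07248144. That is Cycle 1 Day -7 predose for the food-effect subset and Cycle 1 Day 1 predose for everyone else. Bring the sentence defining QTc change into line, and state that the Day -7 ECGs at 1 h and 2 h count as post-baseline.

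Separately, reconcile the passages that use a change from baseline in conduct (Table 3 footnote m, Section 7.1 and Section 8.2.3) with the Section 9.4.5.1 definition for this subset, so that the reference on Day -7 is clear. No threshold or clinical rule is proposed here.

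The cost is about one sentence in each document for the analysis, plus that reconciliation. The Day -7 predose triplicate is already scheduled, so no visit, ECG or participant is added. Readings already taken can be paired correctly at analysis.
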